### Planned analysis

A strength of the study is that each patient will her own control (unexposed status before RT) and evaluations will be based on individual changes of measurements over time. Paired tests for comparisons will be used. All tests will be bilateral with alpha = 5 %. Patients’ baseline characteristics before RT (pre-RT) will be used as "reference" values.(o) Description of the population at baseline (before RT) will be performed including: the medical data collected in the questionnaire, in particular the risk factors for cardiovascular disease; measurements of all biomarkers; 2D-STE measurements including strain and strain rate; CCTA measurements including mean number of coronary segments with plaques. Descriptive statistics (means, standard deviations, percentages and confidence intervals of 95 %) will be used the whole cohort.(i) For the analysis of primary endpoint, the occurrence and progression of early subclinical cardiac lesions will be analyzed based on prevalence study and Chi-square tests.(ii) Wilcoxon tests for paired-samples will be used to study the variations of targeted circulating biomarkers during follow-up. Crude temporal trends will also be considered.(iii) A detailed dose reconstruction will be performed for each woman. CT images used for treatment planning allow delineation of the heart and surrounding organs. However, on these images the coronary arteries are not visible and cannot be delineated. Registration of the planning and coronary angiography CT images will allow delineation of the coronary arteries on the planning CT images. Using the 3D dose matrix associated with the RTDose file generated during treatment planning [38] and the added coronary contours, dose volume histograms and 3D dose maps [28] of the whole heart and coronaries will be generated. This process will be performed with the Isogray treatment planning software (http://www.dosisoft.com/en/rt-planning/tps-isogray/dose-calculation-models.html). A description of the doses thus obtained will be shown for the whole cohort of women.(iv) Spearman correlations will provide results on the association between measurements of strain and strain rate and indices of coronary plaques and the measurement of biomarkers and the radiation dose absorbed by the different structures of the heart. Dose-response relationship between subclinical and dosimetric data will be studied in order to provide results on the effect of dose on subclinical outcome. These relationships will be established from coarse to fine levels, considering first the heart as a whole and going through different substructures. Logistic regression models as well as generalized linear model and repeated data models could be used for the study of the variation between 0 and 2 years the intermediate measurements.(v) For individualized risk for each patient, multivariate model of normal tissue complication probability (NTCP), which takes into account relationships among all parameters will be proposed based on subclinical cardiac lesions occurrence, including clinical, biological and dosimetric data using logistic regression and forward variable selection.

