## Background

It has been shown that adjuvant Radiotherapy (RT) for breast cancer presents a benefit in terms of reducing local recurrence and deaths resulting from breast cancer [1]. However, breast RT can lead to secondary effects due to the presence of neighboring normal tissues within the irradiation field, including the heart. The severity of radiation-induced toxicity to healthy tissues can unfortunately affect the quality of life of cancer survivors.

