### Circulating biomarkers

From a biological point a view, understanding the biological mechanism of the initiation and progression of early radiotherapy side effects on normal tissue such as cardiac tissue is also an important issue. To our knowledge, there are no specific and early biomarkers of radiation-induced heart damage at the present time. According to the dose distributions at heart, ionizing radiation can generate cardiac injury and a major challenge remains the identification of reliable biomarkers that could help to diagnose and predict cardiotoxicity. Depending on the type of injuries (microvascular rarefactions, coronary damage, tissue inflammation) potentially relevant biomarkers are different.

Many classical biomarkers (*C-reactive protein*, *N-terminal pro-B–type natriuretic peptide* (NT-proBNP) and *troponin* (TnI), *…*) were shown to be potential biomarkers for cardiac damage, in particular after radiotherapy [18–20]. Circulating inflammatory cytokins [21] can also sign tissue inflammation. It was also showed that irradiation induces acute endothelial activation or dysfunction that can be observed many weeks after irradiation and resulting in pro-inflammatory endothelial phenotype.

Another hypothesis to explore is that the irradiation may be responsible for an increase in the circulating levels of certain miRNAs expressed by cells of the heart tissue Currently, the potential function of extracellular miRNAs is being studied intensively, and the first studies have confirmed that miRNAs may indeed function in cell-to-cell communication. [22]. Many studies have reported the use of miRNAs as circulating biomarkers for diagnosis or prognosis of cardiovascular diseases. Although many of those studies still require replication in multiple independent study populations, the picture emerges that some plasma miRNAs are quite specific for cardiovascular pathologies and may be useful for diagnostic and monitoring purposes.

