#### The secondary objectives are:

II.Study of the temporal variations of a panel of targeted circulating biomarkers of microvascular rarefactions, coronary damage, and tissue inflammation related with breast RT.III.Evaluate precisely the absorbed doses, for the whole heart and for the different structures of the heart, specifically the coronary arteries.IV.Analyse the dose-response relationship between subclinical cardiac changes, biomarkers, and absorbed doses and propose multivariate model of normal tissue complication probability (NTCP), which takes into account relationships among all these parameters and potentially offer a powerful approach to the optimization of risk assessment.V.Establish a biobank of plasma for further analysis of biomarkers linked to the study of RT cardiotoxicity.

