• Age between 50 and 70 years • Women surgically treated for left or right breast cancer and for whom adjuvant treatment is radiotherapy with irradiation of the breast or chest wall irradiation and possibly ganglion chains, • Adjuvant radiotherapy with 3D CRT performed in Clinique Pasteur Toulouse • WHO performance status ECOG (Eastern Cooperative Oncology Group - index usually used to describe the patient's condition) = 0 or 1 • Being volunteer to participate in the study and having signed the consent form	• Indication of adjuvant chemotherapy • Clinically or radiologically detectable metastasis • Personal history of coronary artery disease or myocardial disease • Personal history of breast cancer or other cancer requiring radiotherapy to the thorax • Patient with controlled infection or severe disease and/or non-hazardous to their participation in the study • Contraindications to injection of iodinated contrast (for CCTA): pregnancy, renal failure, allergy • Pregnancy, lactation • Abnormal echocardiography before radiotherapy: - LVEF <50 % - Longitudinal strain > − 16 % - Longitudinal strain rate <1 %/s - Abnormal wall motion • CCTA before radiotherapy showing that therapeutic management is required (by decision of the radiologist and cardiologist)

*3D CRT* 3D conformal radiation therapy, *WHO* World Health Organisation, *CCTA* coronary computed tomography angiography, *LVEF* left ventricular ejection fraction

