**Fig. 2 Fig2:**
[figure not shown]
15 segments of coronary arteries. LM: Left main coronary artery; LAD: left anterior descending artery; LCX: left cicumflex artery; RCA: right coronary artery. For each segment, the following index are measures: stenosis in % narrowed; presence of calcification; presence of soft plaque (adapted from [41])

**Table 3 Tab3:** List of circulating biomarkers measured in BACCARAT protocol

Classical biomarkers of cardiac injury
C-reactive protein, Troponin I, B-type natriuretic peptide (NT-Pro BNP), beta2-Microglobulin, Galectin 3
Inflammatory cytokines:
Interleukin 6, Interleukin 8, Interleukin 18, TNF-α
Endothelial activation and dysfunction
sVCAM,-1, s-ICAM-1, E-selectin, P-selectin, vWF, PAI-1, Fibrinogen, Thrombomoduline, TGF-β1
Microparticles
CD14(monocytes), CD31(endothelial), CD41(platelets), CD3(lymphocyte), CD235a (erythrocyte)
microRNAs
miR-1, miR-133, miR-208, miR-499, miR-126, miR-130, miR-145, miR-181, miR-150, miR-155, miR-223, miR-17, miR-18, miR-22, miR-34, miR-92, miR-140, miR-182, miR-199, miR-423, miR-590.

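### Analysis (iv) relates biomarkers to cardiac dose alone and without adjustment, so a marker released by other irradiated tissue can appear as a cardiac dose-response

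*Protocol article*

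**What the plan says.** Secondary objective IV sets out to relate subclinical cardiac changes, biomarkers and absorbed doses. Planned analysis (iv) names the method, Spearman correlation, and the quantities: strain, strain rate, plaque indices, "the measurement of biomarkers and the radiation dose absorbed by the different structures of the heart". It moves from the whole heart to substructures. Regression and repeated-data models are mentioned as possibilities, without covariates.

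The dosimetry is also confined to the heart. Secondary objective III is to "Evaluate precisely the absorbed doses, for the whole heart and for the different structures of the heart, specifically the coronary arteries", and under Planned analysis (iii) "dose volume histograms and 3D dose maps [28] of the whole heart and coronaries will be generated". The same paragraph notes that "CT images used for treatment planning allow delineation of the heart and surrounding organs", but no dose to a surrounding organ is carried into any analysis.

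On what else is irradiated, the Background refers to "neighboring normal tissues within the irradiation field, including the heart", and Table 1 admits women having "irradiation of the breast or chest wall irradiation and possibly ganglion chains". On marker specificity, the section on circulating biomarkers says "there are no specific and early biomarkers of radiation-induced heart damage at the present time". Table 3 includes inflammatory cytokines ("Interleukin 6, Interleukin 8, Interleukin 18, TNF-α"), endothelial markers and microparticles.

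**The concern.** A circulating marker carries no record of the tissue that released it. Heart, breast or chest wall and any treated nodal chain are irradiated in the same course, so a rise after radiotherapy may come from any of them. Using each woman as her own control removes stable differences between women, but it does not separate tissues exposed together.

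An unadjusted correlation of marker with heart dose has a cardiac interpretation only if heart dose is unrelated to extra-cardiac irradiation across women. The protocol gives a reason to doubt this. Under Study design and population it says that treating the internal mammary chain can give significant doses whichever side is treated. Nodal treatment also adds irradiated tissue outside the heart, so it could move both doses together.

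At stake is the reading of the marker-dose part of objective IV. A marker of general tissue inflammation could be reported as an early marker of radiation heart damage. This is confounding, and a multiplicity correction would not remove it.

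**Working it through.** **Analysable number.** The plan includes 120 women and expects exclusions of about 10 % and 5 %: 120 × 0.85 = 102. The stated size can be recovered on the strain endpoint. A 5 % change from 16.5 is 0.825, the SD is 2.1, power is 80 % and alpha is 5 % two-sided, so n = 2 × (1.960 + 0.842)² × (2.1/0.825)² ≈ 102, and 102/0.85 = 120. The point does not dispute this figure. It only supplies n = 102.

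**Panel.** Table 3 lists 5 classical markers, 4 cytokines, 9 endothelial markers, 5 microparticles and 21 microRNAs, 44 in all. CRP plus the cytokines, endothelial markers and microparticles make 1 + 4 + 9 + 5 = 19 of 44.

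**Model.** H is heart dose, L is extra-cardiac dose and B is the marker, all on a normal scale. B depends on L only (correlation b) and H has no effect. H and L correlate at ρ. The documents give neither ρ nor b, so both are assumed. The correlation induced between B and H is ρ × b.

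**Approximate check.** The Spearman value is (6/π) × arcsin(ρb/2). Its Fisher z is multiplied by √(99/1.06) and compared with 1.96.
- ρ = 0.3, b = 0.3: ρb = 0.09, Spearman 0.086, z = 0.83, rejection about 13 %.
- ρ = 0.5, b = 0.4: ρb = 0.20, Spearman 0.191, z = 1.87, rejection about 46 %.
- ρ = 0.7, b = 0.4: ρb = 0.28, Spearman 0.268, z = 2.66, rejection about 76 %.

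**Simulation.** n = 102, two-sided 5 %. The last column makes 20 % of women right-sided, with low heart dose but the same extra-cardiac dose. That is a further assumption, so those figures are approximate.

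| ρ (heart, extra-cardiac) | b (marker, extra-cardiac) | False positives, no right-sided women | False positives, 20 % right-sided |
|---|---|---|---|
| 0.3 | 0.3 | 13 % | 9 % |
| 0.5 | 0.4 | 49 % | 26 % |
| 0.7 | 0.4 | 77 % | 45 % |

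At ρ = 0 the rate stays at about 5 %. Over a wider grid without right-sided women (ρ from 0.2 to 0.8, b of 0.3 or 0.5) it runs from about 8 % to 98 %.

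**Effect of adjustment.** A partial Spearman correlation given L brought the false-positive rate to between 4.4 % and 5.8 % in every scenario of the wider grid. This assumes that L is measured and captures the extra-cardiac source.

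**Price of adjustment.** Suppose there is a true cardiac effect (marker-heart correlation 0.3) and no extra-cardiac effect. Power is about 83 % unadjusted. Adjusted for one dose, it is about 72 %, 57 % and 42 % at dose correlations of 0.5, 0.7 and 0.8.

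**The case against.** The strongest reply is that everything depends on a correlation the protocol does not report. If heart dose and extra-cardiac irradiation are unrelated across women, or if extra-cardiac dose hardly varies, there is no artefact. The design may also weaken the link. Right-sided women are included partly because they give lower doses, and breath-hold gating is used in some left-sided women. This stands against any claim that a spurious cardiac dose-response will appear. With right-sided women modelled, the false-positive rate falls substantially but not to 5 %. Gating was not modelled.

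A reader might infer that most of the panel is not heart-specific. The documents do not show this: 21 of the 44 markers are microRNAs, which the protocol motivates partly by their expression in heart tissue, and troponin I and NT-proBNP are also listed. Lung would be an obvious alternative source, but the text never names it.

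A reader might also infer that the artefact passes directly into the NTCP model. Under Planned analysis (v), that model is built on the occurrence of subclinical cardiac lesions, so markers are selected against that outcome and not for their correlation with dose. Analysis (iv) also sets markers beside strain and plaque, which is a partial cardiac check but does not repair the attribution to dose.

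The sentence in (iv) could be parsed as correlating imaging with markers and imaging with dose only. Objective IV, however, includes biomarkers among the quantities related to absorbed dose.

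Finally, covariates are often left to an analysis plan. Here, though, the article fixes the method and restricts both the dosimetry and the exposure to the heart. The left-right comparison is only something that could be done, and it is not tied to biomarkers.

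**Conclusion.** The point holds in a conditional form. As described, analysis (iv) cannot separate cardiac from extra-cardiac release of a non-specific marker. A marker with no cardiac origin can therefore show a cardiac dose-response if the two doses are correlated across women. Under the assumed correlations (0.3 to 0.7 between doses, 0.3 to 0.4 between marker and extra-cardiac dose), the error rate is about 9 % to 45 % with 20 % right-sided women, or 13 % to 77 % without them, against 5 % nominal. It returns to about 5 % if the doses are unrelated.

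It would go too far to conclude that the planned Spearman correlation must be dropped, or that a marker should count as cardiac only if an adjusted test is significant. The power loss shown above means such a rule would discard genuine cardiac markers most often where the doses are most collinear. The matter concerns the interpretation of a secondary objective. It does not touch the primary endpoint or the sample size.

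**What to change.** In Planned analysis (iv), keep the Spearman correlation and add beside it:

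- a partial rank correlation of biomarker change with cardiac dose, adjusted for one extra-cardiac dose or irradiated-volume measure from the same planning dose matrix and for nodal irradiation (yes/no), with its confidence interval;
- the left- against right-sided biomarker change, specified as a supporting contrast;
- the observed correlation between heart dose and the extra-cardiac measure, so that readers can see how much confounding was possible.

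Describe a marker-dose association as cardiac only with reference to the adjusted estimate and its interval, not by a pass/fail significance rule.

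The cost is a few exported values per woman and a change of wording, with no extra visit, sample or patient. Intervals will widen where the doses are collinear. Because internal mammary treatment can itself raise heart dose, adjusting for nodal irradiation also removes some of the heart-dose contrast. That is a reason to show both estimates. The adjustment removes only the confounding captured by the chosen measure.

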The dosimetric work performed in BACCARAT with a degree of precision never reached before is a strength of the study. Effects of specific doses to the whole heart and to specific cardiac substructures have only been assessed in a few studies [4] [30] that revealed the importance of better knowledge for the effects of radiotherapy to critical structures of the heart, including the effect of both radiation dose and volume of the heart exposed. In particular, based on dose reconstructions performed with patient-specific simulation CT scan and CCTA, Moignier et al. [30] showed that use of mean heart dose as surrogate to the coronary doses is not reliable. This patient-specific approach was retained for BACCARAT dosimetry. Consideration of irradiated structures within the heart may prove fruitful for the future and is concordant with recommendations for future studies based on radiation dosimetry that are able to take into account the distribution of dose within the heart (rather than just the mean heart dose) may provide a better prediction of the heart diseases following breast radiotherapy [40, 41]. Moreover, the approach of simultaneous assessment of multiple biomarkers, including microparticules and miRNAs was never performed before and should help to understand some biological mechanisms involved in the radiation-induced cardiac changes.

Provided with the patient’s own biological, clinical and dosimetric parameters, the NTCP models should allow an individualized risk for each patient. These new tools and results developed in the BACCARAT project will allow for the optimization of radiotherapy protocols leading to personalized treatments with increased therapeutic efficacy. It should also improve prediction and prevention of potential lesions to cardiac normal tissues surrounding tumors and ultimately enhance patients’ care and quality of life.

BACCARAT project could finally enhance cardio-oncology that has developed recently to ensure the implementation of primary prevention strategies and screening protocols for early recognition of cardiotoxicity in RT treated patients, as early administration of advanced treatment for signs of cardiac lesions may be crucial. By anticipating the cardiac risk after breast RT, one could reduce the cost for patients care.

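### Forward selection is badly suited to an NTCP model drawn from all parameters (44 listed biomarkers plus doses and risk factors) in about 102 evaluable women

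*Protocol article*

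**What the plan says.** Planned analysis, item (v), sets out a multivariate NTCP model "which takes into account relationships among all parameters will be proposed based on subclinical cardiac lesions occurrence". The data types and the method follow directly: "including clinical, biological and dosimetric data using logistic regression and forward variable selection". Secondary objective IV describes the same model and likewise refers to all the parameters together.

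Table 3, "List of circulating biomarkers measured in BACCARAT protocol", contains five groups of markers. Study procedures has blood taken at four times: before RT, at the end of RT, at 6 months and at 2 years. Planned analysis, items (iii) and (iv), adds doses to the whole heart, its substructures and the coronary arteries. Cardiovascular risk factors are recorded at baseline.

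Sample size calculation gives 120 women, with about 10 % to be excluded for abnormal baseline imaging and about 5 % for later cardiotoxic chemotherapy.

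On the use of the result, the Discussion says that "the NTCP models should allow an individualized risk for each patient", and expects the tools to help optimise radiotherapy protocols.

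**The concern.** The article names the method, the breadth of the candidate pool and the purpose of the model. The choice of forward selection can therefore be judged as stated; it is not a detail left to a fuller document.

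Forward selection tests every remaining candidate at each step and keeps the best. With dozens of candidates and few events, the best one is often best by chance. Its coefficient is then overstated, and the fit measured on the same women looks better than it would in new patients. The set of chosen variables is also unstable.

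At stake is a secondary deliverable that the Discussion presents as a basis for individual risk. A reader could take an AUC in the low 0.70s as useful discrimination, when this procedure can reach that level from noise alone.

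**Working it through.** **Evaluable women.** The stated 120 can be reproduced from the article's strain figures: a 5 % relative change in −16.5 is 0.825, with SD 2.1, two-sided 5 % and 80 % power. The formula is 2 × (1.960 + 0.842)² × 2.1² / 0.825² = 101.7, rounded up to 102; then 102 / 0.85 = 120. Read forwards, 120 × 0.85 = 102 evaluable women (102.6 if the losses are multiplied as 0.90 × 0.95).

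**Candidates.** Table 3: 5 classical + 4 cytokines + 9 endothelial + 5 microparticles + 21 microRNAs = 44, counting each marker once. The number of dose and clinical variables is not given. I assume 0 or 16, so 44 or 60 candidates. Using several time points per marker would add more.

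**Events per candidate.** The event rate is not given; I assume 20–50 %.
- 20 %: 102 × 0.20 = 20.4 events; / 44 = 0.46; / 60 = 0.34.
- 50 %: 102 × 0.50 = 51 events; / 44 = 1.16; / 60 = 0.85.

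**Chance that at least one noise predictor passes.** The only significance level in the article is 5 %. It is stated for tests in general, not as the entry rule for item (v), so its use here is an assumption. For independent candidates:
- 44: 1 − 0.95^44 = 89.5 %.
- 60: 1 − 0.95^60 = 95.4 %.

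**Simulation.** Forward logistic selection by score test, n = 102, all predictors unrelated to the outcome, 1000 runs per row. AUC was computed on the same women and on 2000 new patients. Correlated predictors come in blocks of 6.

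| Candidates | Events | Within-block r | Entry p | Runs giving a model | Mean apparent AUC |
|---|---|---|---|---|---|
| 44 | 30 % | 0 | 0.05 | 89 % | 0.71 |
| 60 | 20 % | 0 | 0.05 | 95 % | 0.80 |
| 60 | 30 % | 0 | 0.05 | 95 % | 0.76 |
| 60 | 50 % | 0 | 0.05 | 95 % | 0.74 |
| 60 | 30 % | 0.5 | 0.05 | 91 % | 0.72 |
| 60 | 30 % | 0.8 | 0.05 | 78 % | 0.67 |
| 44 | 30 % | 0.8 | 0.05 | 69 % | 0.63 |
| 60 | 30 % | 0 | 0.157 (AIC-like) | 100 % | 0.92 |
| 60 | 30 % | 0 | 0.01 | 44 % | 0.59 |
| 60 | 30 % | 0 | 0.05/60 | 4 % | 0.51 |
| 5 | 30 % | 0 | 0.05 | 22 % | 0.53 |

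AUC in new patients was 0.50 in every row. With 60 independent candidates and entry at 0.05, about 4 noise variables were selected on average, and 70–83 % of runs showed an apparent AUC above 0.70.

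Further simulations of the same kind widen the ranges slightly. At entry p<0.05 they become about 90–96 % of runs and AUC 0.69–0.80 for independent predictors, and about 64–81 % and 0.63–0.67 at r = 0.8.

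**The case against.** Several points can fairly be made for the plan.

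- **Entry rule.** The article gives none, and the result depends on it. At p<0.01 the effect is much smaller, and at 0.05/60 it almost disappears. This stands, and the figures are conditional on it. It also works the other way, since an AIC-like rule makes matters worse.
- **Candidate count.** Item (v) does not say that each Table 3 marker enters singly. The paired comparisons and correlations come first and might narrow the field. This stands as a limit on the figure of 44, although the reference to all parameters supports a wide pool. Screening markers against the outcome would not remove the optimism.
- **Correlation.** Markers of one family and doses to adjacent structures are probably correlated, which weakens the effect. This stands and is shown in the range.
- **Internal validation.** A reader might infer that none is planned, and so that the model's apparent discrimination could not be told apart from none. The documents do not support this. A condensed article may leave validation and shrinkage to the full protocol or analysis plan, and proper validation would expose the optimism.
- **24-month biomarkers.** A reader might also infer that samples taken together with the outcome will serve as predictors. Item (v) does not say so.
- **Penalised regression.** It can also be unstable with 20–50 events. This stands, and is why the short list matters at least as much as the penalty.
- **Status.** The model belongs to a secondary objective, and no study procedure applies it to treatment. This limits the consequence but does not make the stated method suitable.

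**Conclusion.** The point holds as a poor choice of method, not as missing detail. Forward selection over a pool this wide, at roughly 0.3–1.2 events per candidate, will in most runs return a model when nothing is predictive, unless the entry rule is much stricter than the conventional 5 %. The apparent AUC then typically averages between 0.63 (44 candidates, strong correlation) and 0.80 (60 independent candidates, 20 % events), against a true 0.50.

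Four inputs are assumptions: entry at p<0.05, an event rate of 20–50 %, 44 to 60 candidates, and within-block correlation between 0 and 0.8. The 44 listed markers, the roughly 102 evaluable women and the selection method come from the article.

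The conclusion is that the method often produces spurious models, not that it always does or that the final model must be worthless. The primary endpoint and the sample size do not depend on it. It should be changed because the Discussion promises individual risk prediction from this model.

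**What to change.** In Planned analysis, item (v):

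1. Replace forward selection over all parameters by penalised logistic regression (for example LASSO or elastic net) on a short candidate list fixed before the outcome data are analysed: cardiac dose, age, the main risk factors and a few biomarkers.
2. Repeat the whole model-building process, including selection and tuning, inside bootstrap or cross-validation. Report optimism-corrected AUC and calibration. If the full protocol already provides for this, a cross-reference is enough.
3. Describe the model as exploratory pending external validation, and soften the Discussion statement on individualised risk to match.

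The cost is a change of wording and some computing time, with no extra patients, visits or assays. The drawbacks are that markers left off the list cannot enter this model, although they can still be described in the other analyses, and that the reported performance will look less favourable.
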